### Eligibility criteria

For the intervention group, eligible participants include antenatal mothers who have provided informed consent and are willing to participate in the neuro-parenting program. These participants will need to be available for follow-up assessments at specified intervals to evaluate the intervention’s impact on early childhood development awareness. The control group will comprise antenatal mothers who are receiving routine antenatal and postnatal care without access to the neuro-parenting intervention; they will also provide informed consent and commit to follow-up visits. Exclusion criteria for both groups will include any mothers with medical conditions that could independently influence neurodevelopmental outcomes, as well as those who may face challenges in completing the follow-up.

**The study will be conducted in three phases namely**,

Preparatory Phase.Implementation Phase.Evaluation Phase.

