#### Implementation phase

This Phase of the study employs a non-randomized intervention design to assess the impact of a targeted multimethod parental educational intervention on antenatal mothers. This phase seeks to provide valuable insights into the practical application and potential benefits of the neuro parenting program. A comparison is made between the intervention group, exposed to the neuro parenting program, and a control group receiving routine care without training sessions. The primary outcomes center around evaluating the percentage of mothers who suspect early childhood developmental disorders including true positive, false positive and false negative ratio. The confirmation of DD will be done using Bayley Scale for Infant Development IV. The study entails a meticulously structured follow-up period, with strategically defined time points to assess the program’s efficacy across critical stages of early development. Assessments will be conducted at birth, six months, and twelve months postpartum to monitor developmental trajectories. By demarcating these specific follow-up intervals, the study ensures a systematic framework for evaluating intervention outcomes, particularly the capacity of mothers to recognize neurodevelopmental indicators and suspect potential developmental disorders. This follow-up design is structured to capture the program’s lasting influence on maternal awareness and accuracy in identifying developmental milestones, offering a precise evaluation of the intervention’s long-term impact. Through targeted assessments, the study will measure both immediate and long-term effects on maternal ability to recognize early developmental cues, providing a focused understanding of the intervention’s effectiveness. Implementation strategies are illustrated in Fig. 1 and the timeline has been depicted in Table 1.

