**Fig. 1 Fig1:**
[figure not shown]
Implementation strategy

**Table 1 Tab1:** Spirit time line

	Enrollment and Allocation					Post Allocation				Endline evaluation		Close Out	
**TIME POINTS**	-t4	-t3	-t2	-t1	t0	t1	t2	t3	t4	t5	t6	t7	t8
Team building	X	X											
Stake holder consultations and ethical proceedings	X	X											
Development of BCC Material			X	X									
Evaluation of BCC			X	X									
Preparation of questionnaire for baseline evaluation			X	X									
Baseline survey of knowledge of antenatal mothers					X								
Recruitment					X	X	X	X	X				
Training to antenatal women in intervention group (2 sessions)						X	X	X	X	X	X		
3rd training session – In postnatal period to intervention group								X	X	X	X		
Evaluation of training						X	X	X	X	X	X		
Interview with control mothers								X	X	X	X		
Endline evaluation of intervention								X	X	X	X		
Data analysis												X	X
Report writing												X	X

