#### Evaluation phase

This phase will assess the effectiveness of training program and the incidence of the DD among children born to mothers who participated in the training program. Mothers will have to undergo at least 2 of the three educational/training sessions.

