### Training and assessment

In this phase, all participants will undergo a thorough assessment of training outcomes. The implementation strategy involves providing participants with a comprehensive questionnaire covering knowledge, awareness, and practices related to identifying early child development delays based on the training module. This questionnaire will be administered after the completion of the training module. Upon concluding all training sessions, a final questionnaire will be developed to gauge participants’ overall knowledge, practice, and understanding of the training’s importance. Descriptive statistics will be calculated to analyse quantitative variables, providing insights into the numerical aspects of the participants’ responses. For quantitative variables, frequencies and percentages will be computed, offering a quantitative overview of the participants’ understanding and practices. To explore the association between variables, the chi-square test will be employed, with a significance level set at 5%.

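### The only test named for this non-randomised comparison is an unadjusted chi-square, which cannot separate a training effect from baseline differences between the arms

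*Protocol article*

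**What the plan says.** Protocol article, Implementation phase: "This Phase of the study employs a non-randomized intervention design to assess the impact" of the training, with a trained group compared against a routine-care group. The primary outcome is the percentage of mothers who suspect a developmental disorder, a yes/no outcome per mother. The Methodology section also calls the study non-randomised and lists centres in several cities.

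Eligibility criteria: for the intervention arm, "eligible participants include antenatal mothers who have provided informed consent and are willing to participate in the neuro-parenting program". For the control arm, "antenatal mothers who are receiving routine antenatal and postnatal care without access to the neuro-parenting intervention". Controls must also consent and commit to follow-up, and the exclusions apply to both arms.

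Training and assessment: "To explore the association between variables, the chi-square test will be employed, with a significance level set at 5" per cent. The Abstract's Methods paragraph names chi-square, as an example of the methods to be used, for both knowledge improvement and early identification of delay. The section on interim and follow-up assigns the yield of detection to descriptive statistics. No matching, stratification, weighting, site term or covariate is mentioned.

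Table 1 schedules a "Baseline survey of knowledge of antenatal mothers" at t0. The article does not say what part it plays in the comparison between arms.

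**The concern.** Randomisation is what entitles a crude comparison of two proportions to be read as a treatment effect, and this study has none. Consent and follow-up commitment are common to both arms, so the difference in entry is narrow: willingness for the programme on one side, lack of access to it on the other. That is still enough to matter. Mothers who want to be taught about developmental warning signs may well watch for and report them more often without any teaching, and noticing such signs is the primary outcome.

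A crude chi-square credits such a difference to the programme. A larger sample does not help, because it narrows the interval around a biased value. At stake is whether a significant result could be attributed to the training at all.

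**Working it through.** The documents give no imbalance between the arms, so the size can only be illustrated. The question is how often a crude chi-square rejects when training does nothing but one binary factor related to the outcome is unequally distributed.

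**Inputs**
- Per arm: 520 planned, 20% dropout (Sample size section), so 520 × 0.8 = 416 analysed.
- Test: two-sided, 5% (Training and assessment).
- Control outcome rate: 5%. *Assumption.* The Sample size section calls its 5% an exposure rate. Using it as the reference proportion does match the plan's arithmetic: odds ratio 2 on 5% gives 9.52%, and (1.960 + 0.842)² × (0.05 × 0.95 + 0.0952 × 0.9048) / (0.0952 − 0.05)² = 512.7, which rounds up to the stated 513. That match is before any allowance for dropout, which is a separate matter.
- Factor's odds ratio on the outcome (1.5, 2, 3) and its prevalence in the intervention versus control arm (60% vs 40%, 70% vs 30%): *assumptions*.

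**Method**
1. Let q0 and q1 be the outcome rates without and with the factor, where odds(q1) = OR × odds(q0). Choose q0 so that the control rate, pC·q1 + (1 − pC)·q0, equals 5%.
2. With no training effect, the intervention-arm rate is a = pI·q1 + (1 − pI)·q0.
3. Crude OR = [a/(1 − a)] / [0.05/0.95].
4. Rejection = 1 − Φ[(1.96·SE0 − d)/SE1] + Φ[(−1.96·SE0 − d)/SE1], where d = a − 0.05, SE0 uses the pooled rate and SE1 the separate rates.

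**Worked case: factor OR 3, 70% vs 30%**
- q0 = 0.0324, q1 = 0.0912. Control check: 0.3 × 0.0912 + 0.7 × 0.0324 = 0.050.
- a = 0.7 × 0.0912 + 0.3 × 0.0324 = 0.0735.
- Crude OR = (0.0735/0.9265)/(0.05/0.95) = 1.51.
- SE0 and SE1 are both about 0.0167, and d = 0.0235. The upper tail is 1 − Φ(0.55), about 0.29; the lower tail is negligible.

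**Results with no training effect**

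| Factor OR | Prevalence, intervention vs control | Crude OR | Rejection, 416 per arm | Rejection, 520 per arm |
|---|---|---|---|---|
| 1.5 | 60% vs 40% | 1.08 | 6% | 6% |
| 1.5 | 70% vs 30% | 1.17 | 8% | 9% |
| 2 | 60% vs 40% | 1.14 | 7% | 8% |
| 2 | 70% vs 30% | 1.31 | 15% | 17% |
| 3 | 60% vs 40% | 1.23 | 10% | 12% |
| 3 | 70% vs 30% | 1.51 | 29% | 35% |

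The nominal figure is 5%. A weak factor does little harm; a strong, uneven one does a lot. The move from 416 to 520 per arm shows that more mothers raise the false rejection rate.

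**Events available for adjustment, same inputs**
- No effect: 416 × (0.05 + 0.05) = 41.6, about 42 events.
- Odds ratio 2: 416 × (0.05 + 0.0952) = 60.4, about 60 events.

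**Approximate precision cost of adjustment**
For a binary covariate, the squared correlation with arm is (0.6 − 0.4)² = 0.04 or (0.7 − 0.3)² = 0.16. The required number rises from 513 to 513/0.96 = 535 or 513/0.84 = 611 per arm, before dropout.

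**The case against.** The strongest reply is that the article does not fix a crude chi-square as the primary between-arm test. The sentence naming it sits in the questionnaire section and speaks only of exploring associations; the Abstract offers it as an example; and a condensed article may leave the adjusted model to a full protocol or analysis plan that is not shown. This stands in part. An unseen plan could add adjustment, and a missing covariate list alone would be no finding. But the Abstract does connect chi-square with early identification, no other inferential method is named, and the method that is named does not suit the stated design. The point is about what the article says.

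Four stronger readings are tempting and are not supported:
- *Controls need only be on routine care.* They must also consent and commit to follow-up. Nor does the text show that mothers choose their arm; controls may lack access because of where or when they attend.
- *Site is confounded with arm.* The text does not say how arms map to sites, and Fig. 1 is not shown. If they coincided, and site had odds ratio 2 on the outcome, the crude odds ratio would be 2.00 and rejection 71% at 416 per arm. That is a possibility the crude test cannot exclude, not a documented fact.
- *The baseline survey goes unused.* Its role is unspecified. A secondary objective on improvement in knowledge suggests that it has some use.
- *The session rule selects the analysed mothers.* The Evaluation phase section says "Mothers will have to undergo at least 2 of the three educational/training sessions", a condition only trained mothers can meet, but not that it defines who is analysed.

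It is also fair to say that the numerical illustration is assumed throughout, and that its mildest case moves rejection only from 5% to 6%.

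**Conclusion.** The concern holds as a mismatch between design and named method. The comparison is non-randomised, entry conditions differ by arm, and the only test named cannot remove baseline differences. It can also mix in site differences, depending on a mapping of arms to sites that the text does not give.

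The size is not known. For a factor with odds ratio 2 to 3 and an imbalance of 60/40 to 70/30, the crude odds ratio is 1.14 to 1.51 with no training effect, and false rejection is about 7% to 29% instead of 5%. This rests on an assumed imbalance, one binary factor, an assumed 5% control outcome rate and 416 mothers analysed per arm. The direction is also assumed: the factor is taken to be commoner among trained mothers. The reverse would hide a real effect.

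**What to change.** Make the primary between-arm analysis of the binary outcome a logistic regression on arm, adjusted for a short prespecified set: site (where both arms are present at a site), baseline knowledge score from the t0 survey, parity and maternal education. If events are few, use propensity-score weighting on the same set. Report the adjusted odds ratio with its 95% confidence interval, and keep the chi-square as descriptive. State in the text how mothers and sites are assigned to arms.

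The cost is a few baseline fields, best collected at enrolment because they may be hard to recover later, and some loss of precision. With only about 42 to 60 events on the assumed inputs, the covariate list must stay short. If arm coincides with site, the model cannot help, and the conclusion must say that the two cannot be separated. Aligning entry by asking every mother before assignment whether she would join the programme would help further, but that changes recruitment in a registered study and is more than an analysis edit.

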### Survey on neurodevelopmental outcomes

Targeting mothers who have attended parental educational interventions, a cross-sectional study will be employed to assess the percentage of mothers suspected of early childhood developmental disorders as a result of the training received.

### Interim and follow-up

Principal investigator will conduct interim analysis, regular follow ups to monitor the progress of the study and make final decision to terminate the trial.

During the follow-ups, participants will be asked to respond to a brief questionnaire addressing outcomes and early red flags identified. Descriptive statistics will then be employed to analyze the yield of early detection by parents alone, particularly focusing on red flags indicative of potential early childhood developmental disorders. This approach ensures a thorough evaluation of the impact of parental educational interventions on the early identification of developmental concerns among participating mothers.

The efficacy or productivity of the instruction is demonstrated through true positive results, as clarified in the outcome. True positives will be determined by comparing the evaluations conducted by parents with those carried out by healthcare professionals such as pediatricians and paediatric physical therapists.

### Evaluation of program effectiveness

At the end of all training sessions, a final questionnaire will assess how much knowledge, practical skill, and understanding participants gained from the program. It will focus on instances where mothers correctly identify developmental concerns, which are then confirmed by healthcare professionals. This evaluation will systematically measure the program’s effectiveness in equipping mothers with the ability to identify developmental disorders with precision. Beyond these direct impacts, the assessment will adopt a holistic approach, evaluating the intervention’s broader influence on multiple domains, including communication, learning, and behavioural development, to provide an in-depth understanding of its effectiveness in supporting comprehensive neurodevelopmental health.

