##### Sample size & sampling methodology

Anticipating a 5% exposure rate to neuro parenting among multigravida women during the study period and aiming for an odds ratio (OR) of 2 with 80% power and 95% confidence interval (CI), with 20% drop out rate the sample size calculation involves recruiting 513 participants per group, rounded to the nearest number, resulting in a total of 520 participants in each arm.

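### The protocol gives two reference standards for a true positive and does not make the reference verdict independent of the mother's report or group

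*Protocol article*

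**What the plan says.** Three sections of the protocol article bear on how a mother's suspicion is judged right or wrong.

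- **Implementation phase.** The primary outcome is the "percentage of mothers who suspect early childhood developmental disorders including true positive, false positive and false negative ratio", and "The confirmation of DD will be done using Bayley Scale for Infant Development IV". The same section says "This Phase of the study employs a non-randomized intervention design" and compares the programme with "a control group receiving routine care without training sessions".
- **Interim and follow-up.** "The efficacy or productivity of the instruction is demonstrated through true positive results", and "True positives will be determined by comparing the evaluations conducted by parents with those carried out by healthcare professionals"; paediatricians and paediatric physical therapists are given as examples. The Bayley is not mentioned here.
- **Evaluation of program effectiveness.** The final questionnaire is to focus on "instances where mothers correctly identify developmental concerns, which are then confirmed by healthcare professionals".

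No section says whether the professional or the Bayley examiner is kept unaware of the mother's suspicion or of her group. None says whether every child is assessed or only those with a reported concern.

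**The concern.** A true positive is only as good as the verdict it is checked against, and here that verdict carries the efficacy conclusion. One section makes it a standardised test, the next a professional's evaluation, and the third a confirmation of something the mother has already raised. Under the last two descriptions the verdict may be formed in the light of her report.

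The groups would not be affected equally. The training teaches mothers to look for red flags, so trained mothers may raise more concerns, both right and wrong. If knowledge of a concern leads the professional to agree with some of the wrong ones, each such case moves from false positive to true positive, and more of them move in the trained arm. The programme would then appear to detect more delay without doing so. Once a verdict has been formed in this way, no analysis can recover the independent one.

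**Working it through.** **The plan's own figures.** The documents give no figure for this bias and no expected true-positive rate. The sample size section is worded as "Anticipating a 5% exposure rate to neuro parenting among multigravida women during the study period", with a target odds ratio of 2. That gives 2 × 0.05 / (0.95 + 2 × 0.05) = 9.52%, a difference of 4.52 percentage points. As worded, this is a difference in exposure, so it is not used as a yardstick below.

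**Step 1: the sections side by side.**

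| Section | Reference verdict | Children it covers |
|---|---|---|
| Implementation phase | Bayley IV | Must include some without a concern, or false negatives cannot be counted |
| Interim and follow-up | Professionals' evaluations, Bayley not mentioned | Not stated |
| Evaluation of program effectiveness | Professionals' confirmation of a raised concern | As worded, those with a concern |

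The standard differs between the first row and the other two. The coverage differs between the first row and the third.

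**Step 2: what the false negative ratio needs.** A false negative is a delayed child whose mother raised no concern. Assume 416 children analysed per arm (520 × 0.8), 10% truly delayed (the background section's figure for India, stated there as a minimum) and 30% of delayed children suspected by their mothers. Each arm then has 41.6 delayed children: 41.6 × 0.3 = 12.5 true positives and 41.6 × 0.7 = 29.1 false negatives. Confirming raised concerns only would find none of the 29.1.

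**Step 3: direction of the bias.** Let *a* be the false-alarm rate among unaffected children, and *f* the share of false alarms wrongly confirmed because the assessor knows of the concern. Then

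- recorded true positives = 0.10 × 0.30 + 0.90 × *a* × *f*
- recorded false positives = 0.90 × *a* × (1 − *f*)
- spurious arm difference = 0.90 × *f* × (*a* trained − *a* control)

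With the same 30% sensitivity in both arms, the training has no true effect on detection. Any difference in true positives comes from *f*.

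**Step 4: size under assumed rates.** Both *a* and *f* are assumptions. The last column is the chance of a significant result favouring the training (two-proportion normal approximation, 416 per arm), against a nominal 2.5%.

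| *a* control / trained | *f* | True positives, control | True positives, trained | Difference (points) | Spurious OR | Chance |
|---|---|---|---|---|---|---|
| any | 0 | 3.00% | 3.00% | 0 | 1.00 | 2.5% |
| 5% / 10% | 5% | 3.225% | 3.45% | 0.225 | 1.07 | 3.8% |
| 5% / 10% | 10% | 3.45% | 3.90% | 0.45 | 1.14 | 5.3% |
| 5% / 10% | 20% | 3.90% | 4.80% | 0.90 | 1.24 | 9.3% |
| 5% / 20% | 5% | 3.225% | 3.90% | 0.675 | 1.22 | 7.6% |
| 5% / 20% | 10% | 3.45% | 4.80% | 1.35 | 1.41 | 16.3% |
| 5% / 20% | 20% | 3.90% | 6.60% | 2.70 | 1.74 | 41.5% |

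False positives fall at the same time. With 5% / 20% and *f* = 10%, they drop from 4.50% to 4.05% in controls and from 18.0% to 16.2% in the trained arm.

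**The case against.** The strongest reply is that the documents are silent on masking and that a condensed article may leave it to the full protocol. The word *then* in the program-effectiveness section gives only an order, and the fix below keeps that order. A masked Bayley examination after a reported concern would fit the text. The professionals' evaluations may themselves be Bayley assessments. The program-effectiveness sentence describes what a final questionnaire will focus on, not an adjudication procedure. The false negative ratio implies that some children without a concern are assessed too. Control mothers are also to receive printed material on neurodevelopmental signs, which may narrow the gap in concerns raised.

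Most of this stands, and it limits the point. A reader might infer that the professional knows the mother's suspicion and probably her arm, that assessment happens only because she raised a concern, and that true positives are therefore inflated. No section says the first, the false negative ratio tells against the second, and the third would require that knowledge to change the verdict, which a standardised instrument may resist.

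The reply does not remove the disagreement between sections. The one that says how true positives are determined does not name the Bayley, and the one that speaks of confirming concerns covers fewer children than the primary outcome needs. Naming the Bayley elsewhere does not settle which verdict counts.

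**Conclusion.** The point holds as an inconsistency in the reference standard for the primary outcome. The sections, read together, leave that standard without stated independence from the mother's report or group. The risk of bias is conditional. If the assessor knows the concern or the arm, and this affects the verdict, true positives may rise and false positives fall in the arm that raises more concerns.

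The size is unknown. Under the assumptions above, the spurious difference runs from 0.225 to 2.70 points and the odds ratio from 1.07 to 1.74. It is nil if the assessor is masked or the scoring is unaffected. Expressing it as a share of the 4.52-point difference would be unsound, because that figure comes from an exposure rate. The change should be made, since it is mainly one of wording and the bias cannot be repaired afterwards.

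**What to change.** Align the three sections on one procedure:

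1. Record the mother's checklist and suspicion, with the date, before the child is assessed.
2. Have the planned Bayley IV scored by an examiner who sees neither her report nor her group.
3. State that this score alone, against a cut-off fixed beforehand, classifies true positives, false positives and false negatives. Professionals' agreement with the mother would not enter the classification.
4. Apply this in both arms, including children whose mothers raised no concern, as the false negative ratio already requires.

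**Cost.** If the Bayley is already meant for all children, the cost is procedure wording and withholding two pieces of information from the examiner. If it was meant only for children with a concern, more assessments are needed. On the assumptions above, concerns arise in 416 × (0.03 + 0.045) = 31 control children and in 416 × (0.03 + 0.09) = 50 to 416 × (0.03 + 0.18) = 87 trained children. That is about 81 to 119 children in total, against 832 if all are assessed. Masking will be imperfect, because some mothers will reveal their concern or their arm.
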